## Methods/Design

The methods and design of the intervention study are described using the Consolidated Standards for Reporting Trials (CONSORT) statement and the extension for reporting cluster randomized controlled trials [15].

### Design

This is a two-arm, multicenter, cluster randomized controlled trial assessing CAT as a nursing intervention in long-term residential patients with SMI. Patients in the intervention group will receive CAT in addition to treatment as usual ((TAU) CAT + TAU) and will be compared to the control group who will only receive TAU. Assessments take place at baseline and every three months thereafter. This study has a duration of one year. For the intervention group, four additional assessments take place at 15, 18, 21 and 24 months in order to investigate the long-term effects.

The Medical Ethics Review Committee of the University Medical Center Groningen in the Netherlands approved the study design, research protocol, information brochure and informed consent procedure (approval number M13.143271). The study is funded by a NutsOhra grant (grant number: 1303–041).

### Recruitment and inclusion of patients

A total of 100 long-term residential patients suffering from SMI will be included in the study. Patients who participated in the pilot study or patients who are under 18 years of age are excluded from participation. There are no other criteria held.

Patients are recruited from the long-stay departments of three institutions in the Netherlands: Lentis Psychiatric Institute (Zuidlaren), Dijk en Duin Psychiatric Institute (Castricum) and GGZ Drenthe (Assen). The departments typically provide long-term pharmacological and psychosocial treatment and focus on rehabilitation and recovery for adult SMI patients. Admitted patients have often insufficiently recovered during several previous hospitalizations and/or periods of sheltered living, and experienced educational, vocational and social problems early in life. The majority of the patients suffer from psychotic disorders. Other diagnoses include severe major depression, personality disorders, bipolar disorder and autism.

Patients are informed about the study by nurses from the concerning department. Patients are informed that participation is voluntary and that they are free to withdraw at any time without providing a reason and without consequence for the usual treatment. Questions can be directed at the nurses or the researchers (contact information is provided in a patient folder). Participants are required to provide written informed consent at baseline.

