### Randomization

With regard to the randomization procedure, several issues were to be considered. Each location employed several nursing teams, with separate offices, patient units and caseloads. Cluster randomization was applied on a nursing team level for each of the three institutions. This resulted in an equal distribution in the number of nursing teams allocated to CAT and TAU within each institution. Not only does this approach prevent contamination between nurses in the intervention and control groups, it also enhances implementation of the intervention since all nurses within each intervention team are trained in CAT and regular nursing meetings can be used for informing colleagues about the progression of the intervention. The nursing teams are randomly allocated to either the intervention or the control group by an independent staff member (without interest in or knowledge about the outcome of the allocation) who blindly draws a ticket from a basket containing a CAT ticket and a blank ticket. No inclusion or exclusion criteria are applied for nurses.

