### Blinding

Blinding will take place at the level of assessors of outcome variables. Blinding of patients and nurses is not possible due to the nature of the intervention. Similarly, blinding of the researcher is not possible due to the researcher’s (APMS) role in the training of nurses and CAT meetings with nurses. Research assistants (psychology students educated to at least bachelors level) are trained to administer the assessments. They are blind to the treatment arm in which the patient is included and do not receive any information with regard to the content and aims of the intervention. Nurses and patients are requested not to disclose any information about the allocation of conditions or the content of the intervention to the students. Students are instructed to inform the researcher immediately when they suspect blinds are broken, in which case the measurement is finished by another student who is still blind to the allocation of the patient. Furthermore, guessing of the allocation group by raters after each assessment will be used to evaluate whether blinding was successful.

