**Table 1 Tab1:** **Schedule of enrollment, interventions and assessments**

	**Study period**									
		**Intervention period**					**Follow-up** ^**b**^			
**Time point** ^**a**^	**< T** _**0**_	**T** _**0**_	**T** _**3**_	**T** _**6**_	**T** _**9**_	**T** _**12**_	**T** _**15**_	**T** _**18**_	**T** _**21**_	**T** _**24**_

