**Enrollment:**										
Randomization	X									
Informed consent		X								

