### Cognitive adaptation training: the intervention

#### Preparation: training of nurses and cognitive adaptation training specialists

To optimize the implementation of CAT and to ensure CAT would be included in the working routine, all nurses in the intervention groups were trained in CAT, though not screened for eligibility. Nurses participate in a didactical group training prior to the recruitment of patients. The training is delivered by the CAT specialists who were trained in CAT by [name], the developer of CAT (APMS and JER). Translated PowerPoint presentations and video demonstrations of [name] serve as the basis of the didactical training, to ensure fidelity to the CAT treatment model. The didactical training includes the theoretical background and principles, assessments, use of the CAT manual, intervention strategies, CAT visits and continuity of the intervention. APMS and JER provided an additional training on assessing the EFA, composing the CAT treatment plan (see below) and continuity of CAT in daily care for the CAT specialists at all intervention locations.

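### Unblinded team nurses inform patients after allocation and CAT training, so entry to each arm and the nurse-rated baseline can depend on allocation, and baseline correction cannot fully remove this

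*Protocol article*

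**What the plan says.** The sequence has to be put together from several sections of the protocol article.

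- **Allocation.** Under Randomization: "Cluster randomization was applied on a nursing team level for each of the three institutions". Teams have their own offices, patient units and caseloads. An independent staff member draws the tickets blindly.
- **Timing.** Table 1 ("Schedule of enrollment, interventions and assessments") marks randomization in the column before T0 and "Informed consent" in the T0 column. The recruitment section agrees: "Participants are required to provide written informed consent at baseline".
- **Training.** The section on preparation states that "all nurses in the intervention groups were trained in CAT", and gives the order: "Nurses participate in a didactical group training prior to the recruitment of patients".
- **Approach to patients.** Under Recruitment and inclusion of patients: "Patients are informed about the study by nurses from the concerning department". The only exclusions are age under 18 and participation in the pilot.
- **Blinding.** "Blinding of patients and nurses is not possible due to the nature of the intervention". Research assistants who assess outcomes are blind and are told nothing of the content or aims of the intervention.
- **Baseline measures.** Under Everyday functioning, the SFS and LSP are completed by a nurse, who in the intervention arm is the CAT case manager. MCAS scores may be adapted after comparison with these questionnaires. Table 1 schedules everyday functioning from T0 on.
- **Analysis.** The statistical analysis section corrects for baseline scores and says that this eliminates the effect of average baseline differences between the groups.

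**The concern.** Randomizing teams makes the teams comparable in expectation. It makes the recruited patients comparable only if recruitment works the same way in both arms. Here the people who introduce the study to patients can know the arm and, in CAT teams, have been trained in the intervention and will deliver it. They may, without any intent, approach residents whom they expect to cooperate, or present the study more warmly. Nurses in control teams will not be delivering CAT to the patients they inform. Patients may also know their unit's arm before they consent.

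A second route runs through the baseline. If knowledge of the arm or CAT training changes how a nurse scores the SFS or LSP at T0, the covariate meant to correct for imbalance is itself affected by allocation.

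At stake is the interpretation of the between-group difference in everyday functioning, the primary outcome. A prognostic difference between recruited groups would appear as a treatment effect, or hide one, and a larger sample would not remove it.

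**Working it through.** **1. Order of events**

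| Step | Time | Source in the protocol article |
|---|---|---|
| Teams randomized | before T0 | Table 1 |
| CAT-team nurses trained | before patient recruitment | Preparation section |
| Patients informed by department nurses | at recruitment | Recruitment section |
| Written consent | T0 | Table 1, Recruitment section |
| T0 SFS and LSP rated by a nurse | T0 | Everyday functioning, Table 1 |

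Two links are inferred. The first is that the informing nurses belong to the allocated teams. The second is that control nurses know their team's arm. Both are well supported: units and caseloads are separate, nurses are stated not to be blind, and only the intervention teams are described as trained.

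**2. What the stated safeguards cover**

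- The blind ticket draw conceals the allocation of teams up to the draw. It does nothing for patients approached afterwards.
- Blinded assistants protect the assessments they make. They do not govern entry and do not complete the SFS or LSP.
- Baseline correction removes the part of a difference that the measured score captures. It leaves traits such as motivation or expected response, and for the SFS and LSP (and an adapted MCAS) the score is taken after allocation and training.

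**3. The plan's own sample size**

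Inputs from Sample size calculation: effect size 0.79, α = 0.05 (taken as two-sided), power 0.9, drop-out 30%. A two-sample t-test needs 34.66, rounded up to 35 per arm. Then 35 / (1 − 0.30) = 50 per arm. Both stated figures reproduce, and this point does not alter them.

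**4. Illustration of what a residual shift would do**

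Assumptions, none of them from the document: no true effect, a difference of b SD left after adjustment, 35 completers per arm, individual-level two-sided t-test at 5%, no clustering.

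Non-centrality = b × √(n/2), with n = 35, so √17.5 = 4.183. The test has 68 degrees of freedom and a critical value of 1.995. The false-positive rate is the probability that a non-central t exceeds that value in either direction.

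| b (SD) | b / 0.79 | Non-centrality | False-positive rate |
|---|---|---|---|
| 0 | 0 | 0 | 5.0% |
| 0.1 | 13% | 0.418 | 7.0% |
| 0.2 | 25% | 0.837 | 13.1% |
| 0.3 | 38% | 1.255 | 23.6% |
| 0.4 | 51% | 1.673 | 37.8% |

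With 50 per arm and b = 0.2, the non-centrality is 0.2 × √25 = 1.0 and the rate is 16.8%. More patients make a fixed bias easier to mistake for an effect.

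**The case against.** The strongest reply has four parts.

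**Room for selection may be small.** With only two exclusions, nurses have little discretion over eligibility. If most residents of the participating teams are needed to reach 100, there is little left to select from. This stands as a limit on size: the number of residents per team is not given. It does not close the route, because broad criteria do not fix whom a nurse approaches or how.

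**The full protocol may deal with it.** The article mentions an ethics-approved research protocol, information brochure and consent procedure. Invitation lists or a neutral leaflet may exist there. This also stands, and the absence of such details from the article is not the point. The point rests on the order of events that the article states, and on its claim for baseline correction.

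**The baseline part is narrow.** It applies directly to the SFS and LSP. The MCAS, which drives the sample size and the cost-effectiveness analysis, is an interview and is reached only where its scores are adapted from nurse questionnaires. That is correct.

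**The illustration has no empirical basis.** The shift is assumed, and the test ignores clustering, repeated measures and baseline adjustment. It shows sensitivity only.

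A reader might also infer that nurses obtain consent. The article says only that they inform patients, that consent is written and given at baseline, and that questions may go to nurses or researchers. It does not say who takes consent.

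**Conclusion.** The point holds as a risk built into the stated design. Randomization, CAT training, and then recruitment by unblinded nurses is an explicit sequence, and none of the stated safeguards acts on patient entry. The T0 SFS and LSP, and the MCAS where adapted, share the exposure. The claim that baseline correction eliminates baseline differences is stronger than the method allows.

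It would be tempting to conclude that the arms are imbalanced or that the trial's result will be biased. The document does not support that: no imbalance is shown and neither its size nor its direction can be estimated. The range of about 7% to 38% is conditional on an assumed residual shift of 0.1 to 0.4 SD, 35 completers per arm and no clustering. The conclusion also rests on the two inferences that the informing nurses belong to the allocated teams and that control nurses know their arm. This is a change that should be made while recruitment is still running, as the Trial status section says it is.

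**What to change.** **Recruitment still to come**

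- List all eligible adult residents of each team. Invite everyone on the list in the same pre-set order, with the same information in both arms.
- Log invited, refused and consented by team. Report the log by arm, separately for patients enrolled before and after the change, since enrollment began in September 2013.
- Do not give the consent talk to the blinded outcome assessors. The Blinding section keeps them uninformed of the content and aims of the intervention, so this would trade one bias for another.

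**Analysis**

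- In the primary model, add age and diagnosis group to the baseline score. Both can be derived from the demographic information collected at T0.
- Add institution if the adjustment for locations announced under Treatment as usual does not already cover it.
- Use executive functioning only as test scores. The fallback for untested patients is the Frontal Systems Behavior Scale, which the CAT case manager fills out, so it has the same weakness as the nurse-rated baseline.
- In the statistical analysis section, replace *eliminate* with *reduce*.

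These covariates do not capture motivation or expected response, so the list and the log carry most of the benefit.

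**Cost.** Some administrative time and possibly slower recruitment. No new patient measurements are needed.

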### Sample size calculation

This sample size is based on a power analysis using the effect size (0.79) calculated from Multnomah Community Ability Scale (MCAS) scores from our pilot study [12]. To detect a significant change in daily functioning measured by the MCAS with α set at 0.05 and a power of 0.9, 35 patients should complete the intervention. Studies have shown that withdrawal from psychosocial interventions in psychiatric patients can be substantial. Therefore we have taken into account a conservative drop-out rate of 30% and will include at least 50 patients in each condition. Analyses are performed when both groups completed the assessments at 12 months and at the study end when follow-up assessments of the intervention group have been completed (24 months).

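### The stated power of 0.9 comes from a calculation for independently randomized patients and makes no allowance for clustering by nursing team

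*Protocol article*

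**What the plan says.** The Design section describes a cluster trial: "This is a two-arm, multicenter, cluster randomized controlled trial assessing CAT as a nursing intervention in long-term residential patients with SMI". The Randomization section names the unit: "Cluster randomization was applied on a nursing team level for each of the three institutions", with equal numbers of teams per arm inside each institution. It says only that each location has several teams. It gives no count and no team size.

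The Sample size calculation section takes its effect size from the pilot, "using the effect size (0.79) calculated from Multnomah Community Ability Scale (MCAS) scores from our pilot study", "with α set at 0.05" and "a power of 0.9, 35 patients should complete the intervention". It then allows for "a conservative drop-out rate of 30% and will include at least 50 patients in each condition". No other input appears there: no intracluster correlation, number or size of teams, design effect or baseline correlation.

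**The concern.** Patients of one nursing team share staff, unit and routines, and in the CAT arm the whole team supports every patient's interventions. Their outcomes are therefore likely to be correlated. Positive correlation within randomized teams inflates the variance of the treatment difference, and a small number of teams limits the degrees of freedom for testing it. A sample size worked out for independent patients ignores both.

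This concerns a figure that the article prints, so it is not a matter of detail left to a fuller document. If the power is overstated, a null result on everyday functioning will be read as coming from a trial with a 90% chance of detecting 0.79 when the chance may have been much lower. The article links its results to guideline recommendations and to institutions' decisions on what care to offer, so that reading matters.

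**Working it through.** **Inputs from the protocol article.** d = 0.79, alpha = 0.05, power = 0.9, 35 completers, 30% drop-out, 50 per arm, 100 in total. Since 0.7 × 50 = 35, the 35 is per arm.

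**Step 1: reproduce the plan's figure.**
- Normal approximation, two-sided: n = 2 × (1.960 + 1.282)² / 0.79² = 33.7 per arm.
- Two-sample t-test, two-sided: n = 34.66 per arm, rounded up to 35. Power is 0.894 at 34 and 0.903 at 35.
- Drop-out: 35 / 0.7 = 50.
- Alternatives that do not give 35: a one-sided two-sample test needs 29, a paired two-sided test 19.

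Both printed numbers come out exactly with a design effect of 1.00, so no clustering allowance can be hidden in them. The only slack is the rounding: 35 / 34.66 = 1.0098. With 12 teams (5.83 completers each) that is used up at an ICC of 0.0098 / 4.83 = 0.002.

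**Step 2: allow for teams.** With K teams in total and 35 completers per arm:
- m = 35 / (K/2)
- DE = 1 + (m − 1) × ICC
- effective n per arm = 35 / DE
- noncentrality = 0.79 × √(effective n / 2)
- power from the noncentral t distribution, with 68 df (patient level) or K − 2 df (team level)

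K and the ICC are assumptions, because the article gives neither.

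Worked case, K = 12, ICC 0.05: m = 5.83; DE = 1 + 4.83 × 0.05 = 1.242; effective n = 35 / 1.242 = 28.2; noncentrality = 0.79 × √14.1 = 2.97. Power is 0.83 with 68 df and 0.76 with 10 df.

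| Teams (K) | ICC | DE | Power, 68 df | Power, K − 2 df |
|---|---|---|---|---|
| any | 0 | 1.00 | 0.90 | 0.70 (K = 6), 0.85 (K = 12) |
| 6 | 0.02 | 1.21 | 0.84 | 0.62 |
| 6 | 0.05 | 1.53 | 0.75 | 0.53 |
| 6 | 0.10 | 2.07 | 0.62 | 0.42 |
| 12 | 0.02 | 1.10 | 0.88 | 0.81 |
| 12 | 0.05 | 1.24 | 0.83 | 0.76 |
| 12 | 0.10 | 1.48 | 0.76 | 0.69 |
| 16 | 0.05 | 1.17 | 0.85 | 0.81 |

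**Step 3: the same shortfall in other terms, at ICC 0.05.**
- The difference detectable with 90% power (K − 2 df) rises from 0.79 to about 0.96 with 12 teams and 1.30 with 6.
- Completers needed per arm by the design effect alone, at the same team size, are 35 × 1.242 = 43.5 (12 teams) and 35 × 1.533 = 53.7 (6 teams). After 30% drop-out that means recruiting 63 and 77 per arm, against the planned 50.

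**The case against.** Four points can be made for the plan.

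1. **Baseline adjustment.** The analysis corrects for baseline scores. If 0.79 is standardized on the raw-score SD, a baseline correlation r raises the effective d to 0.79 / √(1 − r²). With the ICC applied to the adjusted outcome and set at 0.05, power (68 df / K − 2 df) becomes 0.92/0.87 at r = 0.5 and 0.96/0.92 at r = 0.6 for 12 teams, and 0.94/0.91 at r = 0.5 for 16 teams. The loss is then fully recovered in several cases. With 6 teams and K − 2 df it is not: r = 0.6 gives 0.71.
2. **Drop-out may be lower.** If all 50 per arm contributed, 12 teams at ICC 0.05 would give 0.92/0.86 without any adjustment.
3. **The worst figures need 6 teams and K − 2 df.** Six teams means two per institution, which sits less well with several per location than 12 or more does. The article names no df method, and with 6 teams K − 2 df alone takes power from 0.90 to 0.70 at zero ICC.
4. **A condensed article may omit an ICC.**

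The first three stand as limits on the size of the problem, and they mean that the net shortfall cannot be fixed from the article. They do not rescue the printed figure. The calculation claims no gain from baseline adjustment, states no correlation, and uses the drop-out margin in full to get from 35 to 50. The fourth fails because 35 and 50 reproduce exactly without any clustering term.

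**Conclusion.** The concern holds: the power statement is wrong as written for a team-randomized trial and must be corrected. That the calculation ignores clustering is certain from the arithmetic. How much power is lost is not, because it depends on the number of teams, the ICC, the df method and the baseline correlation, none of which the article gives.

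For 35 completers per arm, d = 0.79 and no baseline adjustment, every case examined with a positive ICC falls below 0.90. With 12 teams and ICC 0.02 to 0.10, power is 0.88 to 0.76 (68 df) or 0.81 to 0.69 (10 df). With 6 teams it is 0.84 to 0.62, or 0.62 to 0.42 with 4 df. With many small teams and an ICC near 0.01 the loss is slight: 18 teams give about 0.895 with 68 df and 0.86 with 16 df.

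**What to change.** Keep N = 100. Replace the claim of 0.9 with a short power statement for the design actually used, giving:
- the number of teams randomized per arm and the expected completers per team;
- an ICC range, for example 0.02 to 0.10, with its justification;
- the reference distribution, with degrees of freedom counted on teams;
- the baseline-to-12-month MCAS correlation, if a gain from baseline adjustment is claimed, and whether 0.79 refers to the raw or the adjusted SD;
- the resulting power at 0.79 and the difference detectable with 90% power.

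The sponsor knows the team numbers, and the article reports that recruitment is still under way, so this can be settled before outcomes are analysed. The cost is one paragraph and probably a less favourable figure. It needs no extra patients and no change to trial conduct.

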### Randomization

With regard to the randomization procedure, several issues were to be considered. Each location employed several nursing teams, with separate offices, patient units and caseloads. Cluster randomization was applied on a nursing team level for each of the three institutions. This resulted in an equal distribution in the number of nursing teams allocated to CAT and TAU within each institution. Not only does this approach prevent contamination between nurses in the intervention and control groups, it also enhances implementation of the intervention since all nurses within each intervention team are trained in CAT and regular nursing meetings can be used for informing colleagues about the progression of the intervention. The nursing teams are randomly allocated to either the intervention or the control group by an independent staff member (without interest in or knowledge about the outcome of the allocation) who blindly draws a ticket from a basket containing a CAT ticket and a blank ticket. No inclusion or exclusion criteria are applied for nurses.

